**Fig. 4 Fig4:**
[figure not shown]
Power of the sample in relation to the margin of non-inferiority for maternal mortality and birth complications

For the secondary outcome of improved skilled birth attendance (birth assisted by traditional midwife or physician), the pilot study suggested a rate of 92% in control communities (k-statistic 0.011). Follow-up of 1438 births in each cluster (two clusters per arm) would detect a 6.2% increase in skilled attendance (92.1% to 97.8%) with 80% power at a significance level of 5% (allowing us to set the non-inferiority margin at 15%).

These calculations assume no interaction effects with cluster as unit of primary analysis in unmatched parallel groups and relied on the trial simulator devised by Taylor and Bosch [56].

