The pilot showed that a larger trial would be feasible. It allowed us to adjust the intervention, to design and test questionnaires, to establish the local capacity needed to conduct a larger study, and to identify costs of the intervention. The pilot established the acceptability of the intervention according to three criteria. First, the intervention was safe; the groups with midwives receiving support did not have worse health outcomes and did not report complicated cases related to the intervention (see below). Second, the communities did not react against the recovery of traditions; some previous experience had suggested that some community members, particularly the younger ones, might interpret an intervention to support traditional midwives as an attempt to reduce the services provided by the Government. Third, the staff at the local healthcare centres accepted an increased involvement of midwives with no conflicts which would make the health authorities stop the intervention.

The pilot found similar levels of *pregnancy* complications between women in exposed communities (24/94) and controls (65/252) (OR 0.99, 95%CI 0.52–1.71). It was not intended to measure mortality but, in the event, results were compatible with a positive effect of supporting traditional midwives on reducing *birth* complications (9/91 exposed and 57/248 controls reported birth complications, OR 0.37, 95%CI 0.11–0.73). Women living in the intervention area did not report any neonatal deaths during the last year of the intervention (0/93, compared with 6/254 in control area, chi-square = 2.2, *p* = 0.13). The pilot also suggested advantages for women in terms of skilled birth attendance (92/94 among exposed and 233/253 among controls were assisted by a traditional midwife or physician, OR 3.95, 95%CI 1.0–15.59).

The significantly lower birth complications in intervention communities were likely due to two factors: (1) improved referrals as a result of the intercultural brokerage; and (2) increased use of traditional midwives in the intervention area, resulting in fewer women giving birth without a skilled birth attendant. The pilot demonstrated acceptability of the intervention among the communities and the economical and logistical feasibility of supporting traditional midwifery. The pilot also built local capacity for intercultural and multi-disciplinary research that is scientifically valid and also takes full account of the local cultural context.

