**Fig. 2 Fig2:**
[figure not shown]
Schedule of enrolment, interventions and assessments for the study Safe Birth and Cultural Safety

Control communities receive usual healthcare services. Usual perinatal care for indigenous women in the Montaña region of Guerrero is provided by Western physicians (54.6%), nurses (4.2%) and traditional midwives without external support (20.7%); however, some 20.5% of these women do not have any antenatal care. Among those who received antenatal care, more than 3 out of ten women received less than five antenatal check-ups, the minimum indicated by Mexican standards [37].

In this region, Western physicians (36%), nurses (8%) and traditional midwives without external support (47.9%) provide usual care for childbirth. Some 8.1% of the indigenous women had other or no source of care [37]. Control municipalities have a healthcare centre (*hospital básico comunitario*) in San Luis Acatlán as well as two rural posts (*centro de salud rural* and *unidad de consulta externa*) in Atlixtac. In both cases, healthcare facilities are located in the population centres and provide services for the entire municipality. Women in remote areas need several hours’ walking or travel by gravel road to reach the closest healthcare facility. Regional general hospitals (Ometepec and Tlapa) attend the complicated cases remitted from these communities [38].

The intervention will become obvious to residents in the intervention sites, and some outcomes (particularly social cohesion) could be influenced by knowledge of intervention status. The main outcome indicators (non-inferiority for morbidity and maternal mortality) and other secondary outcomes would be less susceptible to this bias.

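### The skilled-attendance outcome leaves out nurses, so a move from nurse to supported midwife would score as a gain although no woman gains an attendant

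*Protocol article*

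**What the plan says.** The sample size section of the protocol article sizes the trial for a secondary outcome of "improved skilled birth attendance (birth assisted by traditional midwife or physician), the pilot study suggested a rate of 92% in control communities". The planned change is from 92.1% to 97.8%. The pilot study section uses the same two attendant types: "92/94 among exposed and 233/253 among controls were assisted by a traditional midwife or physician".

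The description of usual care for control communities (under The intervention, after Fig. 2) has a finer classification: "In this region, Western physicians (36%), nurses (8%) and traditional midwives without external support (47.9%) provide usual care for childbirth". It then adds: "Some 8.1% of the indigenous women had other or no source of care". Nurses are thus a named usual-care provider, and the residual group is separate from them.

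Nowhere does the article say that the word physician covers nurses, or how a nurse-attended birth is to be scored.

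**The concern.** Under the stated rule there are two ways to fail: to be attended by a nurse, or to have some other attendant or none. These are different events for the woman, and only the second fits what the outcome's name suggests.

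The theory of change under Objectives expects supported midwives to widen their services among women who do not need specialist obstetric care. If some of those women would otherwise have had a nurse, each one turns from failure to success although she was attended either way. The reverse move would score as a loss. A switch between physician and midwife is neutral, so among the listed usual-care providers only nurses are treated this way.

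What is at stake is interpretation. The pilot study section already reads greater midwife use as meaning that fewer women deliver without skilled help. A rise in this outcome cannot support that reading unless nurse-attended births are separated from unattended ones.

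**Working it through.** **Inputs.** Pilot counts: 233/253 controls and 92/94 exposed (The pilot study). Planned rates: 92.1% and 97.8% (Sample size calculation). Regional childbirth providers: physicians 36%, nurses 8%, midwives 47.9%, other or none 8.1% (The intervention, usual care).

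**1. The plan's own figures.** 233/253 = 92.1%, the planning control rate. 92/94 = 97.9%, which the plan gives as 97.8%. Planned gain: 97.8 − 92.1 = 5.7 points; 5.7/92.1 = 6.2%, as stated. The planning rate is therefore the pilot's own rate, under the same wording as the outcome.

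**2. Are nurses a separate category?** 36 + 8 + 47.9 + 8.1 = 100.0%. The regional groups do not overlap and are complete, so nurse births are in neither the physician group nor the residual group.

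**3. Ceiling on the artefact in pilot controls.** Failures under the stated rule: 253 − 233 = 20, and 20/253 = 7.9%. Let f be the share of these 20 that were nurse-attended (not reported). If every nurse birth moved to a midwife and nothing else changed, the outcome would rise by f × 7.9 points. With nurses counted as attended, the control rate is (233 + 20f)/253.

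| Assumed nurse share f | Maximum artefact (points) | Control rate with nurses counted |
|---|---|---|
| 0% | 0 | 92.1% |
| 25% | 2.0 | 94.1% |
| 50% | 4.0 | 96.0% |
| 75% | 5.9 | 98.0% |
| 100% | 7.9 | 100% |

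**4. One anchored value.** If the 20 failures split as in the regional figures, f = 8/(8 + 8.1) = 49.7%. The maximum artefact is 0.497 × 7.9 = 3.9 points, or 3.9/5.7 = 68% of the planned gain, if all nurse births move. If half move, it is 3.9/2 = about 2.0 points.

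**5. What it would take to produce the whole planned gain.** f would have to be at least 5.7/7.9 = 72%. At exactly that share every nurse birth would have to move.

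**6. Headroom after correction.** A 5.7-point gain needs a control rate of at most 100 − 5.7 = 94.3%. That is passed once f exceeds (94.3 − 92.1)/7.9 = 28%. Above that share the planned gain cannot occur, and the detectable difference has to be restated.

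**The case against.** The strongest reply is that this may be only loose wording. The regional rate with nurses included is 36 + 8 + 47.9 = 91.9%, close to the pilot's 92.1%, so the pilot may have counted nurses under physician. Nurse-only births may also simply be rare in these municipalities. The definition appears in brackets in a sample size paragraph of a condensed article, and detailed coding of attendants may sit in a fuller document. The primary outcome of birth complications is untouched.

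Much of this stands, and it limits the severity. It does not remove the point. The article gives the definition twice in the same terms and sizes the outcome on it. If nurses were counted, the published definition is wrong; if they were not, the tilt is real. Either way the rule needs stating.

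Three stronger readings are tempting, and the article does not support them.

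- A reader might infer that the definition clashes with the planning rate, because regional physicians plus midwives give 36 + 47.9 = 83.9%. But 92.1% is the pilot's 233/253 under the same wording. The pilot covered one municipality, Xochistlahuaca, and the usual-care percentages describe the Montaña region. The two rates can differ without contradiction.
- A reader might set the regional 8.0 nurse points against the 5.7-point target and conclude that 5.7/8.0 = 71% substitution would produce the whole effect. That mixes two populations: the target starts from a pilot control group with only 7.9 points of failures of every kind.
- A reader might restate the control rate as 91.9%. Adding nurses to the pilot numerator can only keep or raise 92.1%.

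**Conclusion.** The point holds in a limited form. As written, the outcome puts nurse-attended births with unattended ones and credits a nurse-to-midwife switch as improvement. The direction favours the intervention if midwives draw women from nurses, which the theory of change makes plausible but which no figure in the article measures.

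The size cannot be fixed from the article. For pilot controls the maximum is 0 to 7.9 points, depending on the unreported nurse share, and about 3.9 points under the assumption that the regional 8 : 8.1 split applies there. The planned gain is 5.7 points. These are ceilings that assume every nurse birth moves; they are not estimates. Carrying them to the trial sites further assumes that the other municipalities resemble the pilot.

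Severity is moderate: one secondary outcome is affected, and the primary analysis is not.

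**What to change.** - Define the outcome as birth attended by a physician, nurse or traditional midwife, with failure being other or no attendant.
- Report the full split by attendant type in each arm beside it, so that substitution is visible.
- Recompute the planning control rate from the pilot records under the same rule, and restate the detectable difference from that rate.
- Settle the rule before the arms are compared at follow-up.

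The sponsor should confirm that the questionnaire records nurses separately. The Outcome measures section mentions midwife-attended and unassisted home births and the midwife's presence at institutional births, but does not name nurses.

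The cost is one definition and a recount of 20 pilot control births and 2 exposed ones (94 − 92). The downside is that replacing nurses with midwives no longer counts as a gain, and a higher control rate leaves less room to show improvement.

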### The pilot study

A pilot cluster-RCT tested the feasibility and acceptability of an intervention to support authentic traditional midwives between 2008 and 2012 [27]. The pilot was not powered to determine the effect of the intervention, but it did measure outcomes in the intervention and control group, in order to establish that the intervention was not likely to have an adverse effect on maternal morbidity and mortality.

The pilot study was conducted in Xochistlahuaca municipality with *Nancue ñomndaa* (Amuzgo) communities and included 16 indigenous women clearly considered to be traditional midwives by the communities. These traditional midwives were randomly assigned into two groups, one of which received a co-designed intervention [28].

Each intervention midwife received financial support to pay an apprentice (about US$8 per month); had access to a local birthing centre (purpose-built, rented or loaned); and received logistical support from a male community health worker who could arrange transport for women referred to the local hospital and who could interact with the hospital staff on behalf of the traditional midwives, many of whom could not speak Spanish. Control communities continued receiving usual care, provided mainly by the healthcare centre (*hospital básico comunitario*) located in the municipal capital of Xochistlahuaca and by traditional midwives without external support. An unknown proportion of indigenous women in the rural areas of the municipality did not receive healthcare either from Western health staff or from traditional midwives.

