#### Principal analysis

With 80 communities allocated evenly between the intervention and control arms, the principal analysis of primary outcomes will follow intention-to-treat principles using a cluster *t*-test (everyone included in each cluster, per allocation). We will report outcomes as absolute event rates among intervention and control groups, risk difference with two-sided 95% confidence intervals (95%CIs) and one-sided 97.5% confidence intervals for the non-inferiority analysis, and relative risk reduction (RRR) with 95%CI [48]. The intracluster correlation coefficient (ICC) will be calculated by dividing the between-cluster variance by the variance within and between clusters. 

*Sensitivity analysis* will focus on the different ethnic groups and their accompanying government health services. It will also examine the four intervention components separately because, although all components are available for all participating midwives, we expect a range of implementation in practice.

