### Sample size calculation

Borrowing from the field of bioequivalence, equivalency trials and their statistical testing procedures focus on non-inferiority margins [53]. We expect that supporting traditional midwives does not result in worse primary outcomes of maternal health than does the available usual care in the region, principally because so few indigenous women in the study area access available services. Under the non-inferiority hypothesis, the trial might show equivalent or superior effects of the intervention [54]. The pilot study suggested additional benefits that secondary outcomes accrue from a culturally safe intervention. In the absence of previous studies in similar settings, we established a practical margin for non-inferiority-based discussion of findings with local authorities and indigenous communities. The resulting computation of study power illustrates the possibilities of demonstrating non-inferiority in these small communities of fixed size.

Based on 2013 data, we expected 5752 births across the four municipalities [55]. This study size is too small to use maternal mortality as an outcome over the funded duration of the trial, using 150% as the minimum non-inferiority margin to be detected. For birth complications as primary outcome, this study size can detect differences within a practical margin for non-inferiority of 15%, with 80% power at a significance level of 5% (Fig. 4).

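### The 80% power stated for skilled birth attendance is not reached by a two-sided 5% test on two municipalities per arm: it is about 69% if k = 0.011 is a coefficient of variation and about 29–32% if it is an ICC.

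*Protocol article*

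**What the plan says.** The protocol's Sample size calculation treats skilled birth attendance (by a traditional midwife or a physician) as a secondary outcome. It takes its inputs from the pilot: "the pilot study suggested a rate of 92% in control communities (k-statistic 0.011"). The design is then given as "Follow-up of 1438 births in each cluster (two clusters per arm"), and the conclusion is that this "would detect a 6.2% increase in skilled attendance (92.1% to 97.8%) with 80% power at a significance level of 5" per cent. The closing paragraph says the calculations were made "with cluster as unit of primary analysis in unmatched parallel groups" and relied on a published trial simulator. The total behind the cluster size is also given: "we expected 5752 births across the four municipalities".

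Three other sections bear on the figure:
- Random allocation of the intervention assigns two of the four municipalities to the intervention. It explains that enumeration areas were rejected as the unit because of contamination.
- Principal analysis says "the principal analysis of primary outcomes will follow intention-to-treat principles using a cluster" t-test, with two-sided 95% intervals and one-sided 97.5% intervals for non-inferiority. It introduces this with 80 communities split evenly between the arms.
- On the source of k, "The pilot study was conducted in Xochistlahuaca municipality with" Amuzgo communities only.

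For birth complications, the Sample size calculation claims 80% power at 5% for a 15% non-inferiority margin. The text gives no control risk, no k and no scale for the margin.

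**The concern.** Two randomised clusters per arm leave 2 degrees of freedom for the between-arm comparison. The two-sided 5% critical value is then 4.303 rather than 1.96, and power depends heavily on between-cluster variation. The plan states 80% without saying what kind of quantity k is or whether the 5% is one- or two-sided, and neither standard reading of k returns 80% on the test that the design permits.

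The variance input is also of the wrong kind. Variation among communities within one municipality and one ethnic group cannot show how municipalities differ, and municipalities are what is randomised. The four differ in indigenous group and in health facilities, so the true variation could be larger than 0.011.

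At stake is how an inconclusive result will be read. If no improvement in attendance is shown, readers will judge that against a stated 80% chance of detecting one.

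**Working it through.** **Inputs (Sample size calculation unless noted).** Rates p0 = 0.921 and p1 = 0.978, so d = 0.057 (0.057/0.921 = 6.2% relative). The control rate matches the pilot's 233/253 = 92.1%. Cluster size m = 5752/4 = 1438, which confirms that the cluster in this calculation is the municipality. Clusters per arm c = 2, so df = 2(c − 1) = 2. k = 0.011. Level: two-sided 5%. This is an assumption, taken from Principal analysis, where both interval types put 2.5% in the tail.

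**Formula.** SE² = [p0(1−p0)/m + p1(1−p1)/m + B]/c, where B is the between-cluster variance summed over the two arms. Power comes from the noncentral t distribution with noncentrality d/SE.

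The binomial part is (0.07276 + 0.02152)/1438 = 0.0000656.

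**k as a coefficient of variation.** B = 0.011²(0.921² + 0.978²) = 0.000218. SE = √[(0.0000656 + 0.000218)/2] = 0.0119. d/SE = 4.78.

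**k as an ICC.** B = 0.011(0.07276 + 0.02152) = 0.001037. SE = √[(0.0000656 + 0.001037)/2] = 0.0235. d/SE = 2.43. Equivalently, the design effect is 1 + 1437 × 0.011 = 16.8, leaving 2876/16.8 ≈ 171 effective births per arm.

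**Trying to reproduce the plan's 80%:**

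| Test | Coefficient of variation | ICC |
|---|---|---|
| t, 2 df, two-sided 5% | 68.9% | 28.7% |
| t, 2 df, one-sided 5% | 89.8% | 48.6% |
| Normal, two-sided 5% | 99.8% | 68.0% |
| Normal, one-sided 5% | 99.9% | 78.3% |

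Beta-binomial simulation of the first row gave 69.5% and 32.3%. The only entry near 80% is ICC, one-sided 5%, normal approximation: 78.3%, or 79.2% starting from 92.0%.

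**What 80% would need on 2 df, two-sided.** Either a coefficient of variation of about 0.0087 or an ICC of about 0.0015. With k = 0.011 as a coefficient of variation, the intervention rate detectable with 80% power is about 98.8%, not 97.8%.

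**80 areas as clusters.** With 40 clusters per arm (2876/40 ≈ 72 births each), power exceeds 99.9% on either reading. This does not return 80% either.

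**Birth complications, illustration only.** Assumed: control risk 57/248 = 23% (pilot controls), equal risk in both arms, k = 0.011 carried over from skilled attendance, one-sided 2.5%, 2 df, m = 1438. SE is 0.0114 (coefficient of variation) or 0.0455 (ICC).

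| Margin | Coefficient of variation | ICC |
|---|---|---|
| Relative 15% (0.0345) | d/SE 3.03, power 39% | d/SE 0.76, power 7% |
| Absolute 15 points | d/SE 13.2, power over 99% | d/SE 3.30, power 44% |

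**The case against.** **The two readings of k are not the only ones.** The protocol says only "k-statistic 0.011", with no definition and no sidedness for the 5%. A reader might infer that no reading can give 80% or more. The documents do not support that. On 2 df, a one-sided 5% test with k as a coefficient of variation gives about 90%. Less usual readings, such as a coefficient of variation of the unattended proportion, go higher still. This stands, and it is why the conclusion is tied to two-sided 5% and the two standard readings. Against the one-sided route, nothing under Principal analysis supports a 5% tail.

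**The simulator cannot be inspected.** True. It may have used settings the article does not report. That makes the missing definitions more important; it does not confirm the figure.

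**Principal analysis speaks of 80 communities.** This is a real conflict in the text, but it does not rescue the number. The power statement itself uses two clusters per arm, and the allocation section randomises municipalities.

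**The t-test is named for primary outcomes, and skilled attendance is secondary.** Also true; Secondary analysis mentions multilevel regression. But the power statement declares the cluster as its unit, and a multilevel model does not create more randomised units.

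**The population is fixed, and intervals will be reported.** Both are so. The recomputation therefore changes no recruitment, and the reported intervals do not depend on planned power. The stated 80% still needs correcting.

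**Birth complications.** A reader might infer that power for the primary outcome is 39% or 7%. The text does not allow that conclusion. Control risk, k and margin scale are all assumed here, the figure showing that power curve is not in the copy reviewed, and an absolute margin gives over 99% or 44%.

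**Conclusion.** The concern holds for skilled birth attendance. With two municipalities per arm, 1438 births each, 92.1% to 97.8%, k = 0.011 and a two-sided 5% cluster t-test on 2 degrees of freedom, power is about 69% (coefficient of variation) or about 29–32% (ICC), against a stated 80%. This rests on the two-sided level implied by Principal analysis and on k being one of those two quantities. Because k comes from one municipality, even 69% may be optimistic.

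For birth complications the finding is limited to this: the stated power cannot be checked from the text, and under the illustrative assumptions it runs from 7% to over 99%, depending on the margin scale and the meaning of k.

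**What to change.** 1. State whether k = 0.011 is a coefficient of variation or an ICC, and whether the 5% is one- or two-sided.
2. Recompute the skilled-attendance power with the municipality as the cluster, a t-test on 2 df, and a range of between-municipality variation. The baseline survey covers all four municipalities and can inform the range, but only imprecisely, since four municipalities give 3 degrees of freedom.
3. Replace the 80% with the recomputed values.
4. Reconcile Random allocation of the intervention, Principal analysis and Sample size calculation on the cluster unit: 4 municipalities or 80 communities.
5. For birth complications, state the control risk, k, and whether the 15% margin is relative or absolute, and recompute on the same 2-df basis.

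The cost is recalculation and restated text. No participants are added. On the readings used here, the stated power for skilled attendance becomes less favourable.
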